### Objective

The objective of this study is to investigate the relative effectiveness of augmented durations of CCT on the functional capacity of stroke survivors. Additionally, the study will investigate the effectiveness of augmented duration of CCT on upper and lower extremity functions (with respect to body structure/function, activity limitation and participation restriction) post-stroke and the acceptability of the various CCT durations among stroke survivors. For these to be achieved outcomes of interest will be assessed based on the World Health Organisation International Classification of Function, Disability and Health model (WHO-ICF) [36].

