### Sample size and power calculation

Using power calculations to detect a between-group difference of 42.5 m (0.43 effect size) for a 4-group repeated measure MANOVA in walking distance with 90 % power at α = 0.05, a total sample size of 56 was generated, using an estimated standard deviation (SD) for the calculation as adopted from a meta-analysis [9]. The 42.3 m was proposed as the minimum clinically important difference in walking distance, based on previous studies of implicit measurement error following repeated measurement of speed. The generated total sample size of 56, by implication, will give 14 participants as samples for each group. To incorporate drop-out to follow-up, we hope to recruit a total of 68 participants (17 participants per group). The power calculation was conducted using G*Power version 3.0.10.

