### Data analysis

Data will be recorded in Microsoft Excel before being exported to Statistical Package for Social Science (SPSS). Both descriptive and inferential statistics will be used to examine the outcomes of the study.

Descriptive statistics of frequencies, percentages, mean, and standard deviation will all be used to describe baseline assessments and demographic characteristics of participants. Where appropriate, they will also be used at post-intervention and follow-up to describe relevant findings.

Between-groups relative mean differences of the dependent variables, (spasticity, muscle strength, functional independence, ADL, functional capacity, gait speed, upper extremity function and impairment) will be determined using the general linear model repeated measures, MANCOVA models (for each study domain, adjusted central on baseline as covariates). If the MANCOVA is found to be significant (Roy’s largest root), univariate between-groups results will be reported and pair-wise post hoc analysis will be performed using least significant difference.

A multiple regression analysis will be performed to investigate the relation between improvement at different time periods of CCT and performance in each of the specific dependent variables, to detect which of the durations most effectively predicts improvement in such a variable.

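### The 90 % power is for walking distance tested alone, but walking's between-group result is released only after a joint activity-domain MANCOVA for which no power was calculated.

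*Protocol article*

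**What the plan says.** **Sample size and power calculation.** A difference of 42.5 m, given as an effect size of 0.43, is to be detected "for a 4-group repeated measure MANOVA in walking distance with 90 % power at α = 0.05". This gives 56 in total, 14 per group, raised to 68 to cover drop-out. Only walking distance is named.

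**Objective.** The leading aim is the "relative effectiveness of augmented durations of CCT on the functional capacity of stroke survivors". The other upper and lower extremity functions and acceptability follow as additional aims.

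**Data analysis.** Between-group differences come from repeated-measures MANCOVA models, one for each study domain, with baseline values as covariates. Univariate results and least-significant-difference pairwise comparisons follow only "If the MANCOVA is found to be significant", judged by Roy's largest root in SPSS. A separate multiple regression for each dependent variable asks which CCT duration best predicts improvement.

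**Table 1.** The six-minute walk test (6MWT) is one of six activity measures, with the Modified Rankin Scale, Modified Barthel Index, 10-metre walk test, Action Research Arm Test and Motor Activity Log.

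**The concern.** The power calculation supposes that the four groups are compared directly on walking distance. The analysis plan makes that comparison wait for a joint test that also covers disability, ADL, gait speed and arm use. A walking effect of the planned size could go unreported as a between-group result because the activity measures taken together are not significant.

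The joint test has 3 numerator degrees of freedom per variate. The plan lists constructs rather than scores, so the number of activity variates has to be inferred: five, six or seven are all possible, depending on whether the Motor Activity Log enters and as one score or two. That means 15 to 21 numerator degrees of freedom against 3 for walking alone. The 90 % does not describe this path, and the outcome affected is the one on which the trial was sized.

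**Working it through.** **1. Reproduce the stated sample size.** Inputs from the protocol: effect size 0.43, four groups, three assessments, α = 0.05. Assumptions: 0.43 is Cohen's f, and measurements correlate ρ = 0.5 over time.

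- λ = f² × N × m / (1 + (m − 1)ρ) = 0.1849 × 56 × 3 / 2 = 15.53.
- F test on 3 and 52 df: power 0.905. With N = 55 it is 0.899.

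So 56 is exactly the smallest N for a single-outcome, between-group repeated-measures test.

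**2. What the gate does to the signal.** Let d be the standardised walking effect, δ the vector of effects on all p variates and Σ their correlation matrix. The joint non-centrality is proportional to δ′Σ⁻¹δ. The signal is taken to lie along one contrast of the groups.

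- *Worst case:* the other scales move only through their correlation with walking (δ is d times walking's column of Σ). Then δ′Σ⁻¹δ = d². The joint test has the same 15.53 as walking alone, spread over 15 to 21 df. The joint non-centrality cannot be lower than this.
- *Only walking moves, or all scales move equally, outcomes correlated 0.5:* both multiply the non-centrality by 2p/(p + 1). For p = 6 this is 12/7 = 1.71, giving 26.6.

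**3. Simulated chance that the gate opens and walking's own F test is significant.** N = 56, λ = 15.53, outcome correlation 0.5, five to seven variates, against about 0.90 without a gate:

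| Pattern | Roy, true 5 % critical value | Roy, SPSS upper-bound p-value |
|---|---|---|
| Others move only through correlation (worst case) | 0.54–0.62 | 0.86–0.88 |
| Only walking moves | 0.80–0.85 | about 0.90 |
| All scales move equally | 0.80–0.85 | about 0.90 |

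The low end of each range in the true 5 % column is seven variates and the high end is five.

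**4. Sensitivity, true 5 % Roy gate.**

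- Only walking moves, six variates: 0.59 at outcome correlation 0 (the floor again), 0.70 at 0.3, 0.83 at 0.5.
- Gait speed moves by the same standardised amount as walking, six variates: 0.87–0.90.
- Gait speed moves equally but correlates 0.8 with walking, the others move half as much: 0.60–0.68.
- Worst case with baseline covariates and a non-centrality of 20.7: about 0.65 (six variates) and 0.59 (seven), against about 0.94 for walking alone. This was a smaller simulation (1,200 to 1,500 runs), good to a few points.
- Worst case with all 68 evaluable: 0.72 (six) and 0.68 (seven).

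**5. What the upper-bound Roy gate does under the null.** It opens in about 35 % of trials. Because walking's own F test must also pass, the false-positive rate for walking's overall test on this path is 0.034–0.042, below 5 %.

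**6. The direct alternative.** Average the two post-baseline visits and adjust for baseline, again with ρ = 0.5. The variance factor is (1 + 0.5)/2 − 0.5² = 0.50, so λ = 0.1849 × 56 / 0.50 = 20.7. On 3 and 51 df, power is about 0.97. This is not the test that was sized, but it is at least as powerful under the same assumptions.

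**The case against.** The strongest reply is that the plan as written loses little power. It names SPSS and Roy's largest root. With the upper-bound p-value, walking keeps 0.86 to 0.91, at most about five points below plan. That stands, and so the loss cannot be presented as what the written plan will certainly suffer. But the power survives only because the gate opens in about 35 % of null trials and so hardly acts as a gate. Either it is not a 5 % test, or the 90 % is not the power of the path.

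A reader might infer that the planned effect would be missed about half the time. The documents do not support that. With the named statistic at a true 5 % level, the worst case misses 38 to 46 %. Milder patterns miss 15 to 20 %, and some only about 10 %. Choosing among them needs correlations and effects on the other scales that the protocol does not give.

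A reader might also take the 35 % as walking's own false-positive rate. It is not: that rate is 0.034 to 0.042.

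It would also be too strong to say that walking has no test outside the gate. The per-variable regression does not depend on the MANCOVA. However, it asks which CCT duration predicts improvement; it is not the four-group comparison that was powered, and it has no power statement.

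A separate analysis plan may add detail. But the point is not an omission: the article itself fixes both the single-outcome power and the gate.

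**Conclusion.** The mismatch holds on the text. The 90 % belongs to a direct single-outcome test of walking distance, and the Data analysis section puts that comparison behind a joint test of about five to seven activity variates with no stated power.

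Its size depends on how the gate is run. With a true 5 % Roy gate, the chance of reaching a significant walking result is about 0.54–0.62 in the worst case and about 0.80–0.85 if only walking moves or all scales move equally. With the SPSS default it is about 0.86–0.91, through a gate that barely restricts.

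These figures rest on f = 0.43, correlation 0.5 over time and, in the main table, between outcomes, a signal along one contrast, 56 evaluable participants and an inferred number of variates. The point deserves correction because it concerns the outcome on which the trial was sized and the change is nearly free. It does not show that the trial will fail to detect its planned effect.

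**What to change.** In Data analysis, name the 6MWT as the main outcome and test it at 5 % with its own baseline-adjusted four-group test, not conditional on any MANCOVA. Keep the activity-domain MANCOVA for the remaining activity scales as secondary. The sample-size section can keep 56, with a note that the main test is baseline-adjusted: it is not identical to the test that was sized, but is at least as powerful under the same assumptions.

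If the joint gate is kept for walking distance, restate the power for the gated path, using a statistic and critical value that hold 5 %, and give the assumed correlations and effects on the other scales. In the worst case, regaining 90 % with a true 5 % Roy gate would need about 92 to 100 evaluable participants with six or seven variates.

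Cost: about two sentences and no further participants or data. The activity MANCOVA loses one outcome, and the activity domain gains one further 5 % test. Naming the 6MWT as the single main outcome, with the MANCOVA secondary, deals with that extra test.

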## Abstract

**Background:**

Currently, the key advocacy in neuroscientific studies for stroke rehabilitation is that therapy should be directed towards task specificity performed with multiple repetitions. Circuit Class Therapy (CCT) is well suited to accomplish multiple task-specific activities. However, while repetitive task practice is achievable with circuit class therapy, in stroke survivors repetitive activities may be affected by poor neurologic inputs to motor units, resulting in decreases in discharging rates which consequently may reduce the efficiency of muscular contraction. To accomplish multiple repetitions, stroke survivors may require augmented duration of practice. To date, no study has examined the effect of augmented duration of CCT in stroke rehabilitation, and specifically what duration of CCT is more effective in influencing functional capacity among stroke survivors.

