**Discussion:**

It is expected that the outcome of this study will clarify whether increasing CCT duration leads to better recovery of motor function in stroke survivors.

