## Discussion

Augmenting exercise therapy time to improve recovery outcomes has been supported by some research findings [31–34]. However, the amount of augmented time is not known, using CCT as a delivery model. In this era of evidence-based practice, there is an urgent need to support all facets of implementing CCT with cogent evidence prior to adoption. The *need* to augment the duration of therapy in stroke survivors might not be challenged, but exactly *what* duration (intensity) is suitable, in terms of acceptability and therapeutic benefit to the stroke survivor, needs to be supported empirically.

Reporting the outcome of this study using the ICF model will provide an opportunity to identify which of the domains – body structure/function, activity or participation – will be more responsive to change following intervention, and to which specific duration of intervention.

It is envisaged that engaging in task-specific upper limb practice and task-specific practice involving the lower limb will add credence to this study in explaining which section of these body parts will be functionally better responsive to a particular augmented duration of CCT.

The fact that this study is taking place in a minimally resourced country, will further support the cost benefit of CCT in any setting, and will globalise the empirical findings for CCT.

Finally, if the outcomes of this study support a specific duration of CCT, it will serve as a guide for clinical recommendations in CCT implementation.

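### The regression meant to find the best-predicting duration can only repeat and rank the arm differences, and no stated analysis uses the 60/90/120 min order

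*Protocol article*

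**What the plan says.** Under Data analysis, the protocol article first plans repeated-measures MANCOVA models by study domain, adjusted for baseline. If a model is significant, univariate results follow, with pairwise least-significant-difference (LSD) comparisons. It then adds a multiple regression "to investigate the relation between improvement at different time periods of CCT and performance in each of the specific dependent variables", whose purpose is "to detect which of the durations most effectively predicts improvement in such a variable". For this regression the section states no coding of duration, no significance gate, no interval and no rule for calling one duration better than another.

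The aims are worded in two ways. The Discussion part of the Abstract expects the study to clarify "whether increasing CCT duration leads to better recovery of motor function in stroke survivors", which is a dose-response question. The Background part of the Abstract asks "specifically what duration of CCT is more effective in influencing functional capacity among stroke survivors", and the Objective is "to investigate the relative effectiveness of augmented durations of CCT on the functional capacity of stroke survivors"; these ask which duration is better. On use, the main Discussion says that "if the outcomes of this study support a specific duration of CCT, it will serve as a guide for clinical recommendations".

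**The concern.** Each participant is randomised to one of 60, 90 or 120 min of CCT or to 60 min of standard physiotherapy. The durations are therefore not separate predictors measured on the same person. Entered as categories, they give the arm contrasts again. To ask which one predicts best is then to ask which coefficient is largest, and a largest coefficient exists whether or not duration matters.

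The printed relation, improvement against performance in the same variable, has a second problem. If performance means the follow-up score, it forms part of the improvement score, so the two correlate without any treatment effect.

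The three CCT arms are also ordered and equally spaced, yet no stated analysis uses that order. At stake is a leading duration for each variable, chosen by rank and perhaps carried into recommendations without a measure of its uncertainty.

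**Working it through.** **Inputs.** From Sample size and power calculation: difference 42.5 m, effect size 0.43, 14 per group analysed, 17 recruited, total 56. From Procedures: three assessment times. The SD and the correlation with baseline are not printed, so both are assumptions here.

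**The plan's own figure.** For the between-groups test in a repeated-measures ANOVA, λ = f²·N·m/(1+(m−1)ρ). With f = 0.43, N = 56, m = 3 and ρ = 0.5 (assumed), λ = 0.1849 × 168/2 = 15.5. On 3 and 52 degrees of freedom the power is 0.905; N = 52 gives 0.879. So 56 is reproduced when 0.43 is read as Cohen's f.

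**Two readings of the SD.**
- If 0.43 is the difference divided by the SD, then SD = 42.5/0.43 = 98.8 m.
- If 0.43 is Cohen's f and 42.5 m is the largest gap among four means, the gap is at most 0.43·√8 = 1.216 SD and at least 2 × 0.43 = 0.86 SD. The SD is then between 42.5/1.216 = 35 m and 42.5/0.86 = 49.4 m.

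**Chance gap between the best and worst CCT arms when all three durations are equally effective.** The expected range of three independent normal means is 1.693 standard errors, with standard error SD·√(1−ρ²)/√14. Here ρ is the correlation of follow-up with baseline. At SD 98.8 m and ρ = 0 this is 1.693 × 98.8/3.742 = 44.7 m.

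| SD (m) | ρ | Mean gap (m) | Chance that gap exceeds 42.5 m |
|---|---|---|---|
| 98.8 | 0 | 44.7 | 49% |
| 98.8 | 0.7 | 31.9 | 25% |
| 98.8 | 0.8 | 26.8 | 14% |
| 49.4 | 0 | 22.4 | 6% |
| 49.4 | 0.7 | 16.0 | 0.4% |

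With all 17 per arm retained and SD 98.8 m, the mean gap is 24 to 41 m (ρ from 0.8 to 0). Under equality each duration ranks first with probability 1/3.

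**Ranking when duration does matter.** With a true linear rise of 42.5 m from 60 to 120 min, SD 98.8 m and 14 per arm, 120 min ranks first in 67% to 82% of simulated trials (ρ from 0 to 0.8). Rank alone therefore names another duration in 18% to 33%. If 90 and 120 min are equally good, both 42.5 m above 60 min, the choice between them is close to even.

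**Shared score.** Take improvement as follow-up minus baseline, performance as follow-up, equal variances and no treatment effect. Their correlation is (1−ρ)/√(2(1−ρ)) = √((1−ρ)/2), which is 0.71, 0.50 and 0.32 for ρ = 0, 0.5 and 0.8.

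**Power of a slope over the three CCT arms.** With equal arms the fitted rise from 60 to 120 min equals the 120 v 60 difference, with standard error SD·√(1−ρ²)·√(2/14). At SD 98.8 m and ρ = 0, 42.5/37.3 = 1.14. On 39 degrees of freedom (two-sided 5%) the power is 20%. It is 25% at ρ = 0.5 and 46% at ρ = 0.8. At SD 49.4 m the same rise is 0.86 SD, and the power is 60%, 73% and 96%.

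**The case against.** Four points on the other side carry weight.

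1. Choosing among durations is a declared aim, in the Objective, the Abstract and the main Discussion. A reader might infer that dose-response is the trial's only real question and that the regression therefore misses it. The documents do not support that, because the dose-response wording is one of several statements of aim.
2. A reader might also infer that the effect of duration goes untested. It does not: the gated LSD comparisons include 120 v 60 and 90 v 60. With three equal, evenly spaced arms, the fitted trend from 60 to 120 min is the 120 v 60 difference. What the slope adds is a single prespecified contrast with an interval, not new information.
3. The coding of duration is not stated, and a condensed article may leave it to a fuller document. Numeric coding is not excluded. The criticism of ranked categories and the criticism of the shared score also rest on different readings of one unclear sentence.
4. The recommendation in the main Discussion is conditional on the outcomes supporting a specific duration. Nothing says that the largest coefficient wins whatever its uncertainty. To say that the regression will name a winner from noise is too strong: that is certain only if the durations are equal and rank alone decides.

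What remains is the stated purpose. Even a which-duration aim needs arm differences with intervals and a rule for reading them. Finding the strongest predictor among mutually exclusive allocations supplies neither.

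**Conclusion.** The point holds in a limited form. The regression, as its purpose is written, adds no comparison to the MANCOVA beyond an ungated ranking, and its printed form relates two quantities that share a score. No stated analysis uses the order of the durations, although the Abstract asks whether increasing duration helps.

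The size depends on an SD that the article does not give. At 98.8 m, the chance gap with 14 per arm averages 27 to 45 m (ρ from 0.8 to 0), close to or above the target of 42.5 m at the lower correlations. At about 49 m it averages about 22 m unadjusted and rarely reaches the target. The structural criticism does not depend on the SD; the claim that chance gaps rival the target does.

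A reader might multiply error rates over the eight listed variables to get a large overall false-positive figure. That would need independent outcomes, which is unrealistic for measures on the same patients, so no such figure is relied on here.

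**What to change.** Replace the regression sentence with the following:

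- For each outcome, in the three CCT arms only, regress the follow-up score on its baseline and on allocated duration (60, 90 or 120). Report the slope per 30 min with its 95% confidence interval, and state which follow-up assessment is meant.
- Beside it, show the baseline-adjusted pairwise differences between durations, with 95% intervals.
- Keep 60 min CCT v 60 min standard physiotherapy as a separate contrast. The control differs in type of therapy, not in duration, and does not belong in the slope.
- Label any ranking of durations exploratory, and base no recommended duration on rank alone.

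The cost is a short rewrite, with the same data and software. Two downsides should be stated. A linear slope is less sensitive to a plateau, which is why the pairwise differences stand beside it. Under the 98.8 m assumption, its power for a 42.5 m rise is only about 20% to 46% with 14 per arm, so an interval that includes zero is not evidence of no duration effect. For that reason, and because upper-extremity function is also an objective, claims about duration should not all depend on the walking-distance slope interval excluding zero.

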## Discussion

Augmenting exercise therapy time to improve recovery outcomes has been supported by some research findings [31–34]. However, the amount of augmented time is not known, using CCT as a delivery model. In this era of evidence-based practice, there is an urgent need to support all facets of implementing CCT with cogent evidence prior to adoption. The *need* to augment the duration of therapy in stroke survivors might not be challenged, but exactly *what* duration (intensity) is suitable, in terms of acceptability and therapeutic benefit to the stroke survivor, needs to be supported empirically.

Reporting the outcome of this study using the ICF model will provide an opportunity to identify which of the domains – body structure/function, activity or participation – will be more responsive to change following intervention, and to which specific duration of intervention.

It is envisaged that engaging in task-specific upper limb practice and task-specific practice involving the lower limb will add credence to this study in explaining which section of these body parts will be functionally better responsive to a particular augmented duration of CCT.

The fact that this study is taking place in a minimally resourced country, will further support the cost benefit of CCT in any setting, and will globalise the empirical findings for CCT.

Finally, if the outcomes of this study support a specific duration of CCT, it will serve as a guide for clinical recommendations in CCT implementation.

